**Fig. 1 Fig1:**
[figure not shown]
Schedule of enrolment, interventions, and assessments in this study

### Sample size

Previous studies found 22.4% telangiectasia at two years [9]. We expect the use of a spacer could reduce the skin dose to 50% [21] and the occurrence of any telangiectasia (≥ grade 1) to 7.7% [43]. To test this reduction (e.g. the superiority of the intervention), 105 (Fisher’s exact test) patients per treatment arm would be needed (α = 0.05, β = 0.20). A sample size of 230 patients will allow for a 10% lost to follow-up rate.

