## Methods/design

### Aim and design

We propose a parallel-group RCT comparing the occurrence of telangiectasia at two years in PBSI patients with or without a subcutaneous spacer injection. Allocation ratio is 1:1 and the trial is designed to test the superiority of the intervention. The primary hypothesis for the trial assumes that an injected hyaluronic acid spacer will reduce skin dose of PBSI and eventually the rate of telangiectasia at two years, compared to patients undergoing PBSI without spacer. As the intervention is applied when the patient is sedated, a placebo injection as comparator was deemed unnecessary. The methods section is described according to the Standard Protocol Items: Recommendations for Interventional Trials (SPIRIT) 2013 checklist (see Additional file 1).

Eligible patients will be recruited at hospitals referring patients after breast-conserving surgery for adjuvant radiotherapy at the Erasmus MC Cancer Institute, a large University hospital in Rotterdam, where the PBSI technique can be performed in the Netherlands.

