### Statistical methods

All statistical tests will be two-sided and a *p* value < 0.05 is considered to be significant. Statistical analyses will be performed using IBM SPSS version 24 (IBM Corporation, Armonk, NY, USA). Data will be analyzed following intention-to-treat and per-protocol. Missing data will be handled using multiple imputation. Descriptive statistics will be used for all outcome measures.

A Fisher’s exact test or Chi-squared test will be performed to test the reduction in the rate of telangiectasia in the study groups at two-year follow-up, i.e. to test the hypothesis that the rates of telangiectasia in both study groups are equal (superiority study).

Local recurrence-free survival as well as overall and disease-specific survival rates at five and ten years will be estimated using the Kaplan–Meier method. The local recurrence rate will be reported at five and ten years. A Fisher’s exact test or Chi-squared test will be performed to test the difference in proportions (six-month, one-year and two-year cumulative rate of side effects, skin dose > 90% over at least 1 cm^2^ at post-planning) between groups. (Skin) dosimetry data will be compared using a Mann–Whitney U test or an unpaired Student’s t-test depending of distribution of data. To study the effect of spacer on cosmesis (BCTOS questionnaire) and quality of life (EORTC-QLQ-C30/BR23 and EQ5-D questionnaire) over time, a repeated measurements analysis will be performed (linear mixed model, covariance structure: unstructured) with independent variables time, allocated group, and interaction effects between time and allocated group.

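### Against the plan's own 105 evaluable patients per arm, 230 enrolled covers a loss of 8.7%, not the stated 10% (a minor misstatement that does not threaten power)

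*Protocol article*

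**What the plan says.** The Sample size section of the protocol article gives the assumed rates as "Previous studies found 22.4% telangiectasia at two years [9" in the control arm, and expects the spacer to reduce "the occurrence of any telangiectasia (≥ grade 1) to 7.7% [43". For Fisher's exact test it concludes that 105 "patients per treatment arm would be needed (α = 0.05, β = 0.20"). It then adds: "A sample size of 230 patients will allow for a 10% lost to follow-up rate". The Methods paragraph of the Abstract repeats that last sentence.

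Three other statements bear on the calculation:
- Aim and design: "Allocation ratio is 1:1 and the trial is designed to test the superiority of the intervention".
- Statistical methods, on sidedness: "All statistical tests will be two-sided".
- Statistical methods, on incomplete data: "Missing data will be handled using multiple imputation".

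The article gives no formula for the step from 210 to 230.

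**The concern.** The requirement and the allowance stand in adjacent sentences and can be checked against each other without any outside figure. With equal allocation the requirement is 210 evaluable women. Taking 10% away from 230 should leave at least that number, and it does not.

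The allowance is the yardstick for judging actual attrition, and the primary endpoint is only observed two years after the implant. A reader who takes the sentence at face value would accept 23 losses as leaving the trial at its stated size. In fact the stated size is missed from the 21st loss onward. What is at stake is the accuracy of a published planning figure.

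**Working it through.** **Inputs, all from the protocol article**
- Control rate 22.4%, spacer rate 7.7%, α = 0.05, β = 0.20, 105 per arm, 230 enrolled, 10% loss (Sample size).
- Two-sided testing (Statistical methods).
- 1:1 allocation (Aim and design).

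**Step 1: reproduce the 105.** The usual two-proportion formula has mean rate (0.224 + 0.077)/2 = 0.1505 and difference 0.147:

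n = [1.960 × √(2 × 0.1505 × 0.8495) + 0.842 × √(0.224 × 0.776 + 0.077 × 0.923)]² / 0.147² = 91.7

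The continuity correction, which approximates Fisher's exact test, gives:

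n′ = (n/4) × [1 + √(1 + 4/(n × 0.147))]² = 104.9, so 105 per arm

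The stated requirement reproduces exactly as a two-sided, continuity-corrected figure. The total is 2 × 105 = 210.

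**Step 2: check the loss allowance.**
- Remaining after 10% loss: 230 × 0.90 = 207, or 103.5 per arm. Shortfall: 210 − 207 = 3.
- Loss that leaves exactly 210: 1 − 210/230 = 20/230 = 8.7%.
- Enrolment needed for a full 10% allowance: 210/0.90 = 233.3, so 234 (117 per arm). The stated 230 is 4 lower, or 4/234 = 1.7%.
- The shortcut of adding 10% gives 210 × 1.10 = 231, which 230 also misses, by one.

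**Step 3: check what the shortfall does to power.** Exact power of the two-sided Fisher test at 22.4% versus 7.7% was found by enumerating every pair of outcomes:

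| Evaluable, control/spacer | Exact power |
|---|---|
| 98/98 | 79.2% |
| 99/99 | 79.7% |
| 100/100 | 80.2% |
| 103/103 | 80.8% |
| 104/104 | 81.2% |
| 105/105 | 81.7% |
| 104/103 (207 in all) | 81.8% |
| 103/104 (207 in all) | 84.7% |
| 115/115 (no loss) | 85.6% |

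The two 207 rows differ from each other, and are not below 105/105, because the exact test is discrete. Slightly unequal arms change which tables are significant. The differences between neighbouring rows should not be over-read. The useful result is that every row from 100 per arm upward exceeds 80%.

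The split of losses is unknown, so the extreme was checked as well. If all 23 losses fell in one arm (115 − 23 = 92), power would be 82.8% at 92/115 and 82.9% at 115/92.

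**The case against.** The strongest defence is that the requirement is really 80% power and that 105 is only an approximation to it. Exact enumeration reaches 80% at 100 per arm, so 200/0.9 = 222.2, or 223 enrolled, would be enough at 10% loss. On that reading 230 tolerates up to 1 − 200/230 = 13% loss. This stands as a statement about power. It does not rescue the sentence, because the section names 105 per arm as the number needed and sets the allowance beside it.

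A second defence is rounding. The 10% is a round planning figure, 230 is within 1.7% of 234, and 20 losses are 9.5% of 210 if the allowance is counted on the evaluable number. This stands as a reason to call the point minor. A loss to follow-up rate is ordinarily read as a share of those enrolled, and on that reading the figure is 8.7%.

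A third defence is that multiple imputation means women without a two-year assessment are not simply dropped. That is true of the analysis. But the plan does not give imputation as the basis for its 10%, and an allowance added to the required number treats lost women as lost information.

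A reader might go further and infer that the trial is underpowered at its assumed loss, or must recruit four more women. The documents do not support either inference, because planned power is kept with 207 evaluable. Nor can one say how 230 was reached, since no inflation formula is given and even the add-10% shortcut yields 231.

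**Conclusion.** Wrong as written, minor. Measured against its own 105 per arm, the plan's 230 covers 8.7% loss and not 10%. At 10% it is 3 evaluable women short, equivalent to 4 enrolled. The loss allowance is slightly overstated, but the design is sound on this point: exact Fisher power at the planned rates remains above 80% with 207 evaluable women.

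The arithmetic rests on reading the loss rate as a share of those enrolled and 105 per arm as a count of evaluable women. The power statement rests on the plan's assumed rates of 22.4% and 7.7%, a two-sided test at 0.05, and counting only observed outcomes, with no credit for imputation.

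**What to change.** Keep 230 and replace the loss sentence in the Sample size section and in the Methods paragraph of the Abstract. Suggested wording: 230 patients allow for about 8.7% loss to follow-up while keeping 105 per arm; with 10% loss about 207 (103 to 104 per arm) remain, and exact two-sided Fisher power at the assumed rates is still above 80%.

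A specific power value for 10% loss is best avoided, because it moves with how the losses fall between the arms. The cost is one sentence in two places. Recruitment, the test and the analysis are untouched, and the only visible change is a slightly less generous stated allowance.

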### Recruitment

The Erasmus MC - Cancer Institute treats approximately 1000 patients with adjuvant breast radiotherapy every year. Given the inclusion criteria, it is expected that approximately 20% of these patients are eligible for PBSI. On top of this, referrals from outside the area are also expected specifically for PBSI. This makes it very likely that the required sample size could be recruited in three years.

### Treatment allocation and blinding

After written informed consent and final eligibility check, the radiation oncologist will enroll the patient and randomization will be performed by the department’s independent trial manager. Patients will be randomly allocated to one of the treatment arms (spacer injection or no spacer injection) in a 1:1 allocation ratio, applying a variable block size randomization (block sizes 2, 4, and 6). This concealed allocation will be computer-generated using the online randomization tool ALEA.

Patients will be blinded for the allocated treatment, as the spacer injection is performed under sedation. However, in some cases the patient might see or feel the effect of the spacer injection later. The treating radiation oncologist will be blinded during treatment planning and during the implant of the palladium seeds and be unblinded after the implant to inject the spacer or not using a telephone call with the departments trial manager.

Investigators will be blinded for allocated treatment during assessment of primary endpoint by performing this assessment in a separate visit in which the physician does not have access to the patient’s medical file. Unblinding will be performed if a patient is going (un)planned off-study. In addition, in case of medical emergencies possibly caused by the spacer, unblinding will be performed. In these cases, a patient’s allocated treatment can be unblinded by checking the medical record of the implantation or by contacting the trial management.

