### Outcomes

The primary endpoint of this trial is the occurrence of telangiectasia at two years after PBSI. Assessment is performed by a blinded physician, following the Bentzen’s 4-point scale which is included in the LENT/SOMA questionnaire [34, 35]. This scale is defined as: “none;” grade I, “< 1 cm^2^,” grade II, “1–4 cm^2^;” and grade III, “> 4 cm^2^.” Patients will also be blinded for the allocated treatment. The secondary outcomes include the local recurrence rate at five and ten years, the disease-free and overall survival rates at five years, as well as brachytherapy and spacer injection adverse events (AE) according to the commonly used NCI Common Toxicity Criteria for Adverse Events (CTCAE v 4.03) scale for acute side effects [36], practically occurring within three months of the brachytherapy, and the Radiation Therapy Oncology Group (RTOG)/ European Organisation for Research and Treatment of Cancer (EORTC) scoring systems for late side effects [37], practically occurring after three months. The symptoms include the experience of pain, skin redness, pigmentation, induration, dermatitis, subcutaneous induration, and the occurrence of infection at the site of spacer injection. Additionally, patient-reported outcome measures (PROMs) include the cosmetic result with the Breast Cancer Treatment Outcome Scale (BCTOS) questionnaire [38], using a validated Dutch version which will shortly be published by our group [39] and the health-related Quality of Life using the Dutch version EORTC QLQ-C30 and BR23 questionnaires, version 3 [40]. Ipsilateral breast recurrence must be proven getting a copy of the biopsy or the salvage surgery pathology report. Dosimetry outcomes include the PTV volumes receiving at least 100% or 200% of the prescribed dose (V_100_ and V_200_) as quality assurance for all treatment plans and maximum dose to a small skin volume of 2 mm thickness over 1 cm^2^ (D_0.2cc_) [21, 41] and the presence of a hotspot (isodose ≥ 90%) [42] on 1 cm^2^ of the skin as indicators of skin toxicity risk.

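### Assessor masking is promised for telangiectasia only, so the between-arm tests of the other clinician-graded skin items are open to observer bias of unknown size

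*Protocol article*

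**What the plan says.** The Outcomes section defines the primary endpoint: "The primary endpoint of this trial is the occurrence of telangiectasia at two years after PBSI". It then names the assessor and the scale: "Assessment is performed by a blinded physician, following the Bentzen’s 4-point scale". The section on treatment allocation and blinding explains how that blind is kept: "Investigators will be blinded for allocated treatment during assessment of primary endpoint by performing this assessment in a separate visit". The grader has no medical file to hand on that occasion.

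The secondary adverse events are graded with CTCAE (acute) and RTOG/EORTC (late). Their content is listed in Outcomes: "The symptoms include the experience of pain, skin redness, pigmentation, induration, dermatitis, subcutaneous induration". Infection where the gel was injected completes that list. The same section places data collection at follow-up visits at two months, six months and yearly to five years. It names no masked assessor for these items.

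Two statements show where the allocation is known. The treating radiation oncologist will "be unblinded after the implant to inject the spacer or not using a telephone call with the departments trial manager". When unblinding is called for, "a patient’s allocated treatment can be unblinded by checking the medical record of the implantation or by contacting the trial management".

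Statistical methods specifies a Fisher's exact or chi-squared test of cumulative side-effect rates between groups at six months, one year and two years.

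**The concern.** Redness, pigmentation, induration and dermatitis are graded by a clinician's judgement. The text secures masking for telangiectasia and is silent on these items, although they too are tested between arms. A grader who knows that gel was injected may score induration higher, or redness lower, in that arm. Either would produce a difference in a randomised comparison without any effect of the spacer, or hide one that exists.

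The Discussion concedes that physicians may remember the allocation. It sets this aside because the primary outcome is assessed at two years and because Bentzen's scale is objective. Neither argument carries over. The tests at six months and one year come sooner after the implant, and these items are not graded on Bentzen's measured area. At stake is how far a difference in secondary skin toxicity can be credited to the spacer.

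**Working it through.** **Masking, outcome by outcome**

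| Outcome | Masking stated in the article | Tested between arms |
|---|---|---|
| Telangiectasia at two years | Masked physician, separate visit, no file | Yes (primary) |
| Redness, pigmentation, skin and subcutaneous induration, dermatitis | No masked assessor stated | Yes, as side-effect rates at six months, one year and two years |
| Patient-reported cosmesis and quality of life | Patients nominally blinded | Yes (mixed model) |
| Skin dosimetry | Dose measure, not a clinical grade | Yes |

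The gap lies in the second row.

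**The plan's own figure (it supplies only the arm size used below)**

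Inputs from Sample size and Statistical methods: 22.4% versus 7.7%, two-sided α = 0.05, power 80%.

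- Mean rate (0.224 + 0.077)/2 = 0.1505; difference Δ = 0.147.
- Uncorrected: n = [1.960·√(2 × 0.1505 × 0.8495) + 0.842·√(0.224 × 0.776 + 0.077 × 0.923)]² / 0.147² = 1.981/0.02161 ≈ 91.7, so 92 per arm.
- Continuity-corrected: (91.7/4) × [1 + √(1 + 4/(91.7 × 0.147))]² ≈ 104.9, so 105 per arm, as stated.
- Exact two-sided Fisher power at 105 per arm: 81.7%.

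**Illustration of the bias**

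The article gives no rates for the secondary skin items. The base rates and shifts here are assumptions. There is no true difference, and knowledge of allocation changes the recorded rate in the spacer arm only.

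Method: P(reject) = Σ over (x, y) of Bin(x; 105, p) × Bin(y; 105, p + δ) × 1[two-sided Fisher p < 0.05], by full enumeration.

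| True rate p (both arms) | δ = 0 | δ = +5 points | δ = +10 points |
|---|---|---|---|
| 10% | 2.9% | 14.3% | 45.6% |
| 20% | 3.4% | 10.8% | 33.3% |
| 40% | 3.7% | 8.7% | 25.2% |

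Downward shifts at p = 20% give 11.8% (−5 points) and 45.6% (−10 points).

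On a base of 20%, 5 points is a quarter of the events (5/20) and 10 points is half (10/20), which is substantial mis-scoring. Milder bias does less. Relative under-recording of 10%, 20% and 30% in the spacer arm gives 4.5%, 8.5% and 16.2% at p = 20%, and 7.3%, 19.0% and 39.7% at p = 40%.

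**The case against.** Four objections have weight.

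1. A reader might infer that the file lies open at routine visits and that the masked visit serves telangiectasia alone. The article states neither. It says how the primary endpoint is masked, and it does not exclude that other items are graded at the same visit. The sentence on the implantation record concerns unblinding for patients going off-study or in emergencies. It shows that the allocation is recorded, not that graders look it up. The full protocol or the CRF (Additional file 2) may name a masked assessor. This stands, so the point is limited to what the text promises.

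2. A reader might infer that the trial relies on these signs to separate radiation toxicity from spacer toxicity. On its natural reading, the Discussion ties that separation to skin dose. Of the symptoms it says only that effects on them can be analysed. The stronger reading is not supported.

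3. A masked two-year grade might seem able to replace the two-year comparison now planned. It cannot. The planned quantity is a cumulative rate, whereas one examination gives prevalence on that day and misses effects that came and went.

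4. Exposure is probably greatest early. The spacer is expected to degrade over 3–9 months and may be palpable, so an examiner at two or six months might detect it without the file. A masked two-year grade does not repair those earlier comparisons.

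These are also secondary outcomes, and the Discussion already admits that the design is not fully double-blind. That admission, however, is defended for the primary outcome only. It neither masks nor labels the other tests.

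**Conclusion.** The point holds in limited form. As written, the article promises assessor masking for the primary endpoint only, while it tests clinician-graded skin items between arms in a setting where the treating oncologist knows the allocation and the record contains it. Those comparisons are open to observer bias in either direction.

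The documents do not allow the size to be estimated. Under the assumed 20% rate, the chance of a spurious significant result per comparison runs from 4.5% with 10% relative under-recording to 33.3% with a 10-point upward shift, against 3.4% without bias. It would be too strong to say that a difference in late skin effects could not be attributed to the spacer: the bias is possible, not shown.

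The primary endpoint, sample size, dosimetry and patient-reported outcomes are untouched. The change is worth making because it is cheap, and because a masked grade cannot be obtained after the visit has passed.

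**What to change.** - **Treatment allocation and blinding:** have the masked physician at the existing separate two-year visit also grade redness, pigmentation, skin and subcutaneous induration and dermatitis before any access to the file.
- **Statistical methods:** add a between-arm comparison of this masked two-year point prevalence alongside the two-year cumulative rate, not in place of it.
- **Labelling:** describe the six-month, one-year and cumulative side-effect comparisons as not assessor-masked, and interpret them accordingly.
- **If it is already so:** where the full protocol or CRF assigns these items to the masked physician, state that in the blinding section.

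Cost: a few minutes and a few CRF lines per patient, and one more analysis per item, with the same assessor and no new visit. Scores before two years remain unmasked. The sample size does not change.

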### Interventions

The permanent seed implant procedure includes a computed tomography (CT) simulation done positioning the patient similarly to for external beam breast radiotherapy. The clinical target volume (CTV) corresponds to the seroma with a 1-cm margin, limited to the fascia pectoralis, and 5 mm below the skin; the planned target volume (PTV) is an additional expansion of 0.5 cm with the same skin and chest wall limits. A pre-implant plan is generated using the MIM Symphony® software (MIM Software Inc., Cleveland, OH, USA) to order stranded ^103^Pd seeds of 2.5 U activity.

For the procedure, anesthesia includes a non-steroidal anti-inflammatory drug (NSAID) for two days, light sedation with Propofol, and local freezing. Patients are positioned on a breast board, with the arm abducted similarly to the CT simulation. The breast skin is disinfected and the patient draped. The PTV projection perpendicular to the fiducial needle axis is outlined on the skin surface and verified using ultrasound. A PBSI template (Concure Oncology, Seattle, WA, USA) is attached to the fiducial needle and immobilized using a modified medical articulated arm (Fisso, Medtec Baitella Alt, Switzerland). The preloaded needles containing ^103^Pd strands are then inserted under US guidance [33]. In patients allocated to receive spacer, an amount of 4–10 cc of biodegradable hyaluronic acid (Barrigel™, Palette Life Sciences, Santa Barbara, CA, USA or Restylane SubQ®, Galderma Benelux, Breda, the Netherlands) is injected directly under the skin under ultrasound guidance covering the PTV projection, aiming to create an extra 0.5–1 cm space between the treatment volume and the skin. If the skin is judged not to be at risk in all projection quadrants, it could be decided to only inject the area at risk. The injected skin quadrants will be reported specifically. All radiation oncologists involved in this study are trained to perform the intervention and the injection procedure and reporting instructions are incorporated in trial protocols. The hyaluronic acid spacer is expected to be fully degraded after 3–9 months.

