A drawback of our study is that we are not able to secure a full double-blind design. Patients might be aware of an injected spacer as it could be palpable under the skin. For physicians, it might be possible to remember the allocated treatment after being unblinded during the PBSI procedure. However, with the assessment of the primary outcome at two-year follow-up, this memory effect is not likely to cause any bias. Also, the type of outcome measure (telangiectasia using Bentzen’s 4-point scale) allows for an objective, reproducible assessment. Furthermore, this a single-center study and our findings should be confirmed in a multicenter setting. Lastly, with only patients undergoing PBSI in this study, generalization of our findings to other APBI techniques should be done with caution. However, theoretically, this principle would hold for any APBI technique with a rapid dose fall off.

In this trial, we investigate the effect of a subcutaneous spacer injection on the skin dose, late skin toxicity, and cosmetic outcome in patients treated with PBSI in the setting of breast-conserving therapy. Our results will be relevant for most forms of breast brachytherapy as well as robotic radiosurgery, as skin spacers could be used to protect the skin with these other techniques.

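### Blinding of the two-year telangiectasia grade rests on a separate visit without the file; nothing stated keeps the physician who injected the spacer from giving it

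*Protocol article*

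**What the plan says.** All references are to the protocol article.

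- **Who grades.** Outcomes: "Assessment is performed by a blinded physician, following the Bentzen’s 4-point scale". The scale runs from none through grade I (under 1 cm²) and grade II (1–4 cm²) to grade III (over 4 cm²).
- **How the grader is kept blind.** Treatment allocation and blinding: investigators are to be kept blind for the primary endpoint by "performing this assessment in a separate visit in which the physician does not have access" to the medical file. No other measure is given.
- **Who learns the allocation.** Same section: the treating radiation oncologist is blinded during planning and seed implantation, and will then "be unblinded after the implant to inject the spacer or not using a telephone call with the departments trial manager".
- **Who could be that physician.** Interventions: "All radiation oncologists involved in this study are trained to perform the intervention". The number of oncologists is not given, and the trial has a single center.
- **What the authors concede.** Discussion: "For physicians, it might be possible to remember the allocated treatment after being unblinded during the PBSI procedure".
- **How they answer it.** Discussion: "with the assessment of the primary outcome at two-year follow-up, this memory effect is not likely to cause any bias". They add that the type of outcome measure permits objective and reproducible assessment.
- **What counts as an event.** Sample size: any telangiectasia, grade 1 or above. Background: in breast radiotherapy studies most lesions are grade 1.

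**The concern.** Outcomes describes the grader as blinded. The stated mechanism blinds only someone who does not already know the allocation. For the physician who took the telephone call and injected, or did not inject, the spacer, a visit without the file hides nothing except a reminder. The Discussion's reply to the memory problem is needed only if a physician unblinded at the implant may later grade the same patient, so the article itself treats that as possible.

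This matters because there is no placebo injection, and the article accepts that some patients may see or feel the spacer. Assessor blinding is therefore the main protection of the primary endpoint. The endpoint is also dichotomized at its most judgement-dependent boundary, none versus a lesion under 1 cm². If an aware grader resolves doubtful cases according to expectation, the error differs between arms. The analysis cannot remove it afterwards.

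**Working it through.** **1. The passages side by side.** Unblinding of the treating oncologist is certain, because it is part of the procedure. Assessor blinding is secured by two things, a separate visit and no file. Neither restricts who the assessor is. The Discussion then defends the design against physicians' memory. Together these give a stated mechanism that does not by itself deliver the blinded physician named in Outcomes.

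**2. The plan's own figure.** Inputs from Sample size and Statistical methods: 22.4% versus 7.7%, two-sided α = 0.05, β = 0.20, Fisher's exact test. The two-proportion formula with continuity correction gives 105 per arm (92 without the correction), and exact Fisher power at 105 per arm, by full enumeration, is 81.7%. The stated 105 is reproduced. This point does not change the sample size.

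**3. How much an aware grader could matter.** The documents give no figure for misgrading, so this is an illustration over a range.

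Assumptions:
- no true effect, with a true rate of 22.4% in both arms (the plan's control rate);
- 80% of lesions are grade 1 (the article says only that they are the majority);
- a share *s* of spacer-arm assessments is made by a grader aware of the allocation;
- an aware grader scores a share *u* of grade 1 spacer-arm lesions as none;
- control-arm grading is unaffected.

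Formula: observed spacer-arm rate = 0.224 × (1 − *s* × *u* × 0.8).

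The false-positive rate is the sum of the binomial probabilities of all outcome pairs with two-sided Fisher p < 0.05, at 105 per arm.

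| *s* (aware) | *u* (under-called) | Lesions lost, *s* × *u* × 0.8 | Observed spacer-arm rate | False-positive rate |
|---|---|---|---|---|
| 0 | – | 0% | 22.4% | 3.5% |
| 1 | 10% | 8% | 20.6% | 4.3% |
| 1/2 | 20% | 8% | 20.6% | 4.3% |
| 1/3 | 30% | 8% | 20.6% | 4.3% |
| 1/2 | 30% | 12% | 19.7% | 5.5% |
| 1 | 30% | 24% | 17.0% | 12.6% |

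The third, fourth and fifth columns depend only on the product *s* × *u*, so the three middle rows agree.

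**4. Direction.** The assumed error only ever favors the spacer. Counting only rejections in its favor, the rate is 1.7% with no bias, 5.0% with half aware and 30% under-called, and 12.5% with all aware and 30% under-called. The nominal share in that direction is 2.5%, half of 5%.

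**The case against.** The strongest reply is that the authors have disclosed and argued this. They say a fully double-blind design cannot be secured, they name the memory effect, and they list safeguards: a separate visit, no file, a two-year interval and an area-based scale. A roster of who examines whom is also detail that an article may leave to the full protocol. Part of this stands. The limitation is disclosed, and the full protocol may say more. But the article does more than stay silent. It states its mechanism, concedes the weakness and defends it by the passage of time. The scale argument carries less weight where the event is any lesion at all and most lesions are small.

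Three stronger readings are tempting, and the documents do not support them.

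- *That the injecting physician will grade her or his own patients.* The article leaves this possible. It does not say that it is planned or frequent.
- *That a physician would have felt the gel at the two- or six-month visit.* The article mentions only patients seeing or feeling it, and does not say who conducts those visits. It expects full degradation within 3–9 months, so no gel should remain as a cue at two years. The documented route for the physician is memory.
- *That the type I error is materially inflated.* The largest figure above needs every grader to be aware and to under-call 30% of small lesions. Milder inputs give 4.3% to 5.5%, partly because Fisher's test starts at 3.5%. The direction of the bias is itself assumed.

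**Conclusion.** The point holds as a weakness in a stated method, worth correcting because correction is cheap. The article calls the grader blinded but does not exclude the one physician who certainly knows the allocation, and it relies on memory fading instead. The size of any resulting bias is unknown. On the assumptions above, the two-sided false-positive rate runs from 4.3% under mild misgrading to 12.6% in the extreme case, against 3.5% with none. The 22.4% and 105 per arm are the plan's figures; the 80% grade 1 share, the under-calling rates and the shares of aware graders are not. A reader should not infer that the trial's result will be biased, only that the design as described does not rule it out.

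**What to change.** In Treatment allocation and blinding, add that the two-year telangiectasia grade is given by a trial physician who did not perform or attend that patient's implant or injection. Where the existing roster allows, the grader should also not have seen her at earlier follow-up visits. This can be done by swapping patients among the radiation oncologists already in the study. Keep the separate visit and the withheld file. Add one CRF item in which the assessor records the believed allocation after grading, so that the success of blinding can be reported.

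The cost is a scheduling constraint and that one item. Treatment, sample size and primary test are unchanged. Because the number of oncologists is not stated, only the exclusion concerning the implant and injection should be mandatory; excluding everyone seen at earlier visits could exhaust a single center's pool. The rule does not stop a patient who knows her allocation from telling the grader, and the believed-allocation item would help to show that. The first patient was enrolled on 8 September 2017, so no two-year grade fell due before September 2019. When the article appeared in December 2018, the rule could still have covered every primary assessment.
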